# A Community-enabled Readiness for first 1000 Days Learning Ecosystem (CRADLE) for first-time families: study protocol of a three-arm randomised controlled trial

**DOI:** 10.1186/s13063-021-05144-5

**Published:** 2021-03-06

**Keywords:** Choice architecture, First-time parent, Midwife, Nudge, Randomised controlled trial, Self-efficacy

## Abstract

**Background:**

Enhanced parenting self-efficacy (PSE) contributes to positive parenting and future parental-child health. First-time parents, in particular, are in need of support since the pregnancy until post-delivery to strengthen their early PSE. However, there is a lack of effective and sustainable relevant programmes in the community. The Community-enabled Readiness for first 1000 Days Learning Ecosystem (CRADLE) aims to develop a self-learning eco-community throughout the pregnancy and early childhood to promote PSE among first-time parents. We apply choice architecture strategy using behavioural nudges and midwife-led continuity care during the first 1000 days, and test their effects on PSE and mother-child health for first-time families in Singapore.

**Methods:**

This three-arm randomised controlled trial will recruit up to 750 pregnant women from the KK Women’s and Children’s Hospital, Singapore. Participants will be randomly assigned to receive: (1) standard routine care; (2) behavioural nudges (text messages) along with the use of a social media platform; or (3) midwife-led continuity care involving individualised teleconferencing sessions, during pregnancy and post-delivery. Using web-based questionnaires, participants will be assessed for baseline socio-demography and health status in the first visit, with follow-up assessments in the third trimester, at birth, 6-week (primary end-point), 6-, 12-, 18- and 24-month post-delivery. The primary outcome is PSE. Secondary outcomes include health and birth experience, mental wellness, feeding practice, maternal and child nutritional status. Intention-to-treat and per-protocol analyses will be performed using general linear models to test the effects of interventions across three arms. Recruitment has begun in June 2020 and is estimated to complete in September 2022.

**Discussion:**

This study may identify a sustainable effective strategy in the community by helping first-time parents to have a positive experience during the pregnancy, childbirth and parenthood, leading to an enhanced PSE and health outcomes for both mother and child. Findings from this study will provide insight into the implementation of early parenting and mother-child care programmes.

**Trial registration:**

ClinicalTrials.gov NCT04275765. Registered on 19 February 2020.

**Supplementary Information:**

The online version contains supplementary material available at 10.1186/s13063-021-05144-5.

## Background

The “Developmental Origins of Health and Disease (DOHaD)” paradigm underlies the influences of early-life environment on health and disease development over the lifespan [1, 2]. Strong evidence in humans have shown optimal nurturing during pregnancy and after delivery for both mother and child, which are critically important to build an optimal foundation for subsequent long-term maternal-child health [3, 4]. These involve ensuring an optimal psychological and physical health across the pregnancy, lactation and early childhood, as covered by the window of the first 1000 days of life, i.e. 280 days of gestation plus 730 days of the first two postnatal years [5]. The DOHaD or the first 1000 days concept is not just about academic science, but also about education, policy making and everyday practice for individuals [3]. However, to date, most recommendations for pregnant women and young children have yet to take long-term health consequences of early life condition into account [4].

Mental wellness and nutrition, serve as the key components in the psychological and physical health. With the onset of pregnancy, there is a great need to ensure that expectant parents are mentally and physically well prepared to cope with the developing pregnancy, the childbirth and the new life with their babies [6]. On top of building a nurturing environment, this paves the way to promote and enhance early parenting self-efficacy (PSE), as evidenced by the positive link between prenatal mental wellbeing and PSE [7]. PSE, defined as parents’ belief in their ability to perform the parenting role successfully [8], has emerged as an important clinical target for intervention due to its impact on parent and child wellbeing [9]. High PSE is related to effective parenting [10] and great parental competency [11]; low PSE appears to be a salient risk factor of parental depression [12, 13] and is closely linked to long-term harm in child physical and mental development [14–16]. Improving early PSE is thus important towards building a healthy environment for children and for parents, promoting long-term positive health outcomes.

Bandura summarised several factors that could impinge on PSE, including the lack of social support, parental depression, and temperamentally difficult infant and child health problems [17]. This is particularly relevant to first-time families where low PSE is often seen among first-time parents [18]. Specifically, first-time mothers tend to experience difficulties and are vulnerable to emotional distress due to the uncertainties, maladjustments and new challenges faced, including antenatal requirements/demands, intense lifestyle changes, adaptation as a new parent, physical and financial burden, during both pregnancy and postpartum periods [19–21]. The lack of experience, knowledge and skills in antenatal care, childbirth, breastfeeding, infant care and coping strategies have placed them in great needs to acquire social and professional supports [6, 22, 23]. This highlights the importance of having an engaged effective support for these first-time mothers since the onset of pregnancy to promote their self-efficacy in parenting.

In this digital era, though first-time expectant parents could receive much information via the internet, parental education offered by health care professionals remains relevant due to the need of a trustworthy source of information that can be relied on [24]. Delivery of education through midwives during the antenatal and postpartum periods has shown to be useful, making those parents felt supported and prepared for parenting [24–26], with an increased PSE reported [27]. As reviewed, midwife-led continuity care starting from pregnancy until early parenting period has been associated with positive maternal outcomes and parents’ satisfaction [28]. Importantly, the resulted positive maternal outcomes had contributed to reduced health care cost [29]. Unfortunately, in Singapore, there is no midwife-led continuity care service to help first-time parents in gaining positive parenting experience and building PSE. To scale up the service to make it accessible to people, community-based midwifery care is required.

A simple, cost-effective approach which has shown positive effect on parenting is the provision of parental education by health care professionals through digital platforms. A recent web-based psychoeducational intervention over 6 months post-delivery has shown to improve PSE, reduce postnatal depression and enhance social support among first-time mothers in Singapore [30]. A text messaging programme over 1 year for parents of pre-schoolers in the United States was found to be effective in supporting positive parenting practices [31]. The text messages serve as a powerful nudging tool by targeting behavioural barriers to good parenting [32]. Through messages, the complexity of parenting was broken down into small steps that are easy-to-achieve, along with continuous reinforcement and encouragement to help parents change their parenting behaviours and practices [33]. The use of nudges represents a choice architecture strategy which is widely used in public policy making, to alter people’s behaviour and influence decision making [33–35].

### Aims

The main goal of the Community-enabled Readiness for first 1000 Days Learning Ecosystem (CRADLE) study is to promote and sustain healthy behaviour both for the mother and offspring in the first 1000 days and beyond, through a supportive community-led sharing environment for first-time families. To achieve the goal, we developed a virtual interactive and sharing platform, integrated with choice architecture using calibrated nudges, along with midwife-led care service. Our target is to create a self-learning ecosystem by providing knowledge support and guidance, via interactions with health care professionals and peer learning through e-platform. This will in turn create opportunities for the participants to become empowered and eventually develop as community volunteers for maternity care.

Specifically, we aim to examine the effects on PSE and health outcomes in mother and child, with the use of behavioural nudges in the form of text messages (a choice architecture technique) and midwife-led care service, from pregnancy until the first 2 years post-delivery. We hypothesise that during the first 1000 days, the use of virtual nudging tool in the form of text messages supplemented with social media, or physical care from midwives supplemented with individualised teleconferencing sessions will lead to a better maternal PSE, health and birth experience, mental wellness, and nutritional outcomes in both mother-child, compared with those who are receiving standard routine care. The framework of the study is shown in Fig. 1.

**Fig. 1 Fig1:**
[figure not shown]
Study framework

## Methods/design

### Trial design

CRADLE is conceptualised as a three-arm, parallel-group, non-blinded randomised control trial (RCT). The allocation ratio of the control group to two intervention groups is 1:1:1. The three arms comprise: (1) standard routine care; (2) behavioural nudges (text messages) along with the use of a social media platform; (3) midwife-led continuity care involving individualised teleconferencing sessions. The protocol has followed the SPIRIT guidelines (see Additional file 1). The trial registration number of the study is ClinicalTrials.gov NCT04275765.

The flow of the trial is shown in Fig. 2. Following informed consent at the recruitment visit, a baseline assessment on maternal sociodemographic characteristics and health status will be conducted, followed by randomisation to the control or intervention group (Arm 2 or 3) using the electronic randomisation list. Depending on the follow-up time-point (i.e. 30-week, at birth, 6-week, 6-, 12-, 18-, and 24-month post-delivery), every participant is required to complete few sets of online questionnaires for assessments on PSE, health and birth experience, mental wellness and feeding practice. A 2-week timeframe is given to the participants to complete the questionnaires, depending on their preferable schedule and availability within the period. Maternal and child anthropometric measures including weight and height are also assessed. Details of study measures and questionnaires used according to the visit time points are presented in Table 1.

**Fig. 2 Fig2:**
[figure not shown]
Study flowchart

**Table 1 Tab1:** Data collection and study instruments

	Baseline visit	Third trimester	Birth	6 weeks	6 months	12 months	18 months	24 months
**Socio-demography**								
Age	√							
Ethnicity	√							
Family structure	√							
Education	√							
**Health and birth experience**								
PROMIS Global-10 scale^*^	√	√			√		√	
Birth Satisfaction Scale-Revised^*^			√					
**Mental wellness**								
Patient Health Questionaire-2^*^	√	√		√	√			
Edinburgh Postnatal Depression Scale	√	√		√	√			
**Nutrition**								
Breastfeeding success			√	√	√			
Breastfeeding confidence			√					
Breastfeeding Self-Efficacy Score-Short Form^*^			√	√	√			
Infant Feeding Questionnaire							√	
Maternal and child weight/height	√	√	√	√	√	√	√	√
**Parenting self-efficacy**								
TOPSE^*^				√	√	√	√	√
Parental Sense of Competence Scale^*^				√	√	√	√	√
**Medical records retrieval**								
Obstetric and delivery outcomes			√					

*From the International Consortium for Health Outcomes Measurement (ICHOM) Standard Set of Outcome Measures for Pregnancy and Childbirth

*PROMIS* Patient-Reported Outcomes Measurement Information System, *TOPSE* Tool to measure Parenting Self-Efficacy

### Recruitment

Recruitment is conducted at the KK Women’s and Children’s Hospital (KKH), Singapore. In this study, we target to recruit up to 750 pregnant women visiting antenatal clinics of KKH during their early pregnancy. Recruitment brochures, posters and banners that contain general information and selection criteria of the study are placed at different locations, such as hospital lifts and clinics. Interested women self-contact the study team by email or phone, or to be referred by doctors or nurses.

Inclusion criteria are women who meet the following: first-time pregnant mother, aged 17 years and above, going to reside in Singapore for the next 3 years, able to understand English (or with a family member who is able to assist), and to provide written, informed consent. Exclusion criteria are women with medical conditions such as serious chronic diseases and high risk complicated pregnancies. Throughout the study period, participants who experience loss of pregnancy, perinatal demise, congenital abnormalities in offspring, serious medical events in mother/child, unable to comply with study protocol or wish to discontinue their participation will be withdrawn from the study. For participants who withdraw from the study, consent will be sought to retain and analyse their data until the withdrawal time-point.

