#### Primary outcome

The primary outcome of this RCT is PSE, measured using the Tool to measure Parenting Self-Efficacy (TOPSE) and the Parental Sense of Competence Scale (PSOC) at 6-week as the primary endpoint, followed by 6-, 12-, 18- and 24-month post-delivery. We include both TOPSE and PSOC, as the combination use of these two tools provides a comprehensive measure on the domain-specific and domain-general self-efficacy components. In addition, we are able to evaluate, following suggestions by Bandura [36], any differences in employing two assessment strategies operating at different levels of specificity [8].

The TOPSE is a multidimensional, self-report measure designed to assess parents’ perceived ability to parent their children, which took into account the views and experience of parents from a range of cultural and social backgrounds [37, 38]. The theoretical underpinning of TOPSE is based on self-efficacy theory developed by Bandura [36, 39]. It consists of 48 items which are divided into eight subsections: (1) emotion and affection, (2) play and enjoyment, (3) empathy and understanding, (4) control, (5) discipline and setting boundaries, (6) pressures, (7) self-acceptance and (8) learning and knowledge. Participants will be requested to rate items using a 11-point Likert scale ranging from 0 (completely disagree) to 10 (completely agree). The higher the score, the higher the level of PSE.

The PSOC is a self-report instrument designed to measure parenting satisfaction and efficacy [40]. It is a domain-general measure with items describing common parental ideas regardless of the child’s age and the specific tasks that the parent has to face [40]. Although the PSOC has mainly been used in parents with children, it has been found to be valid for use in parents with infants [41, 42]. It consists of 17 items scored on a 6-point Likert scale ranging from 1 (strongly disagree) to 6 (strongly agree). The higher the score, the higher the level of parenting satisfaction and self-efficacy.

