### Statistical analysis

One-way analysis of variance (ANOVA) and chi-square tests or Fisher’s exact tests will be used to compare differences in baseline characteristics among the three arms. The primary analysis will be according to the intention-to-treat principle, i.e. all participants who were assigned to a condition. Differences in outcomes across three arms at each time-point will be compared using the one-way analysis of covariance (ANCOVA) (General Linear Model, GLM), adjusting for baseline characteristics and measures. Bonferroni correction will be performed for pair-wise comparisons. Linear mixed models will be used to compare the outcomes across time points among the three arms, adjusting for baseline characteristics and measures. Additionally, a priori sensitivity analysis will be conducted for complete cases, i.e. participants with complete follow-up and data. There are no formal planned interim analyses of the primary outcome, but progress reports on all data issues will be presented to investigators of the study team. The level of statistical significance will be set at 0.05 (two-tailed) and 95% confidence intervals will be calculated.

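### Randomised women withdrawn before 6 weeks for non-compliance, serious medical events or a child anomaly have no primary outcome, which conflicts with the stated intention-to-treat analysis and can bias it

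*Protocol article*

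**What the plan says.** Randomisation takes place at the recruitment visit in early pregnancy, after consent and baseline assessment: "followed by randomisation to the control or intervention group (Arm 2 or 3) using the electronic randomisation list" (Trial design). Every later withdrawal is therefore post-randomisation.

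The Recruitment section sets the withdrawal rule for the whole study period. It covers "participants who experience loss of pregnancy, perinatal demise, congenital abnormalities in offspring, serious medical events in mother/child", and adds those "unable to comply with study protocol or wish to discontinue their participation will be withdrawn from the study". Withdrawal is from the study, not only from the intervention. For these women, "consent will be sought to retain and analyse their data until the withdrawal time-point".

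The Primary outcome section measures TOPSE and PSOC "at 6-week as the primary endpoint, followed by 6-, 12-, 18- and 24-month post-delivery". Table 1 shows neither instrument at any earlier visit.

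The Statistical analysis section states: "The primary analysis will be according to the intention-to-treat principle, i.e. all participants who were assigned to a condition". The only sensitivity analysis it names is "a priori sensitivity analysis will be conducted for complete cases, i.e. participants with complete follow-up and data".

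**The concern.** An intention-to-treat comparison needs outcomes, as far as they can be had, from everyone randomised. Here the protocol itself ends outcome collection for some of those women, for reasons other than their own wish. Two of these reasons, illness in the mother or child and difficulty in keeping to the protocol, plausibly go with lower parenting self-efficacy. The Background itself lists parental depression and child health problems among the factors that affect it.

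Two things are at stake. Outcomes that could have been collected are lost. And if the women lost differ between arms in number or in outcome, the retained groups are no longer comparable as randomised. An analysis plan cannot fully repair this. A woman with no TOPSE or PSOC value gives neither the ANCOVA nor the mixed model an observation of the primary outcome. Imputation would replace her missing value with an assumption.

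**Working it through.** **Which women lose the primary outcome**

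| Time of withdrawal | Data that may be kept (with consent) | Primary outcome at 6 weeks |
|---|---|---|
| Pregnancy, birth or up to 6 weeks | Baseline and any earlier questionnaires, none of them TOPSE or PSOC | None |
| After 6 weeks | Includes TOPSE and PSOC at 6 weeks | Kept; later time points lost |

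The conflict with the intention-to-treat statement therefore concerns the first row for the primary endpoint, and both rows for later time points. The complete-case analysis leaves out the women in both rows, so it does not test the effect of the rule.

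**Which reasons are avoidable**

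- After pregnancy loss or perinatal death there is no child to rate parenting for, so the outcome is not defined.
- A woman's own wish to leave must be respected.
- Inability to comply, a serious medical event and a congenital abnormality do not by themselves prevent her from answering an online questionnaire.

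**Size of a possible bias**

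The documents give no withdrawal share by arm and no outcome difference for withdrawn women, so there is no figure of the plan's to reproduce. The inputs *w* and *g* below are assumptions. From the protocol come the target difference d = 0.35 and the 250 randomised per arm (Sample size).

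Let *w* be the share of an arm withdrawn before 6 weeks, and *g* the amount in SD by which withdrawn women score below retained women. If the full-arm mean is M and the retained mean is R, then

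M = (1 − w)R + w(R − g) = R − wg, so R = M + wg.

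With the same gap in both arms, bias = (w_intervention − w_control) × g.

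| Assumed withdrawal, intervention vs control | g = 0.3 | g = 0.5 | Share of d = 0.35 |
|---|---|---|---|
| 5% vs 5% | 0 | 0 | 0 |
| 10% vs 5% | 0.05 × 0.3 = 0.015 SD | 0.05 × 0.5 = 0.025 SD | 4% to 7% |
| 20% vs 5% | 0.15 × 0.3 = 0.045 SD | 0.15 × 0.5 = 0.075 SD | 13% to 21% |
| 5% vs 10% | −0.015 SD | −0.025 SD | −4% to −7% |

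**Effect on type I error**

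Take no true effect, 250 randomised per arm, no other losses, and a single comparison at an unadjusted two-sided 5%. The standard error is √[1/(250(1 − w_intervention)) + 1/(250(1 − w_control))], which is 0.093 SD at 10% versus 5% and 0.096 SD at 20% versus 5%. By normal approximation the type I error is 5.3% to 5.8% in the first case and 7.6% to 12.2% in the second.

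**The case against.** A reader might infer that removal is differential by design, because routine care gives Arm 1 no intervention to fail to comply with. The text does not support this. The rule refers to the study protocol, not the intervention, and covers all arms. Arm 1 also has questionnaires to return within two weeks and measurements to attend. Arm 2 is largely passive: messages are sent to the women, enrolment in the group is automatic, and posting is only encouraged. Arm 3 is the one with scheduled contacts that can be missed. It is therefore not shown that removal falls mainly on the intervention arms, or that it inflates both effects.

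Nor do the documents suggest that serious medical events or anomalies will differ by arm; the ethics section expects no adverse health effect. If these withdrawals are balanced, with the same outcome gap, they narrow the population without biasing the comparison.

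It would also go too far to say that the intention-to-treat set becomes nearly a per-protocol set. The abstract names the two analyses separately, and women withdrawn after 6 weeks can keep their primary endpoint.

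Finally, inability to comply may be meant narrowly. Under Data monitoring, an unreturned questionnaire leads to contact from staff, not to withdrawal, and the full protocol may define the term.

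All of this limits the claim about bias. It does not remove the conflict: the published rule ends participation in the study for women whom the analysis section says will be included.

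**Conclusion.** The point holds as an internal conflict with avoidable loss of outcomes and a possible, unquantified bias. The withdrawal rule and the intention-to-treat statement cannot both be met for women withdrawn before 6 weeks, and the number of such women is unknown.

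Unequal withdrawal is plausible because the trial is unblinded and the arms ask different things of participants, most clearly Arm 3. The documents establish neither its presence nor its direction. Under the assumptions shown, the bias runs from 0 to 0.075 SD, and it is negative if control women are withdrawn more. An assumed 20% versus 0% split would give 0.06 to 0.10 SD (0.20 × 0.3 to 0.20 × 0.5), or 17% to 29% of d = 0.35. That is not a fair central case, because the rule applies to the control arm too.

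Severity: should be fixed. Outcomes not collected now cannot be recovered later.

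**What to change.** Reconcile the Recruitment and Statistical analysis sections by separating two events: stopping the assigned intervention, and stopping outcome collection. When the intervention stops remains a matter for the study team and is not addressed here.

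- End outcome collection only when the woman withdraws consent to it, or when pregnancy loss or perinatal death leaves no child to rate parenting for.
- Keep sending the existing online questionnaires to all other randomised women who agree, including those who cannot keep to the protocol, those with a serious medical event in mother or child, and those whose child has a congenital abnormality.
- Analyse them in the arm to which they were assigned.
- Report withdrawals by arm, by reason, and by whether they came before or after the 6-week assessment. Report pregnancy loss and perinatal death separately.

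Cost: a change of protocol wording, some extra staff reminders (Data monitoring already has staff contact non-responders), and possibly renewed consent from women already enrolled, which the ethics section provides for. The questionnaires are already online, so no new instrument is needed.
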